#### Data management

The collection and storage of data will be done according to Good Clinical Practice Guidelines. All study staff involved in the collection or entry of data will be trained by the trial coordinator and will complete ethical conduct of research training (Tri-Council Policy Statement: Ethical Conduct of Research Involving Humans 2). Data from potential and enrolled participants will be stored in the secure platform, Research Electronic Data Capture (REDCap), and a password-protected database on a secure server managed by the Canadian College of Naturopathic Medicine. Data collected at each study visit will be captured using an electronic case report form, which will be entered into the database. Questionnaire completion will be done by the study participants through REDCap. Laboratory data will be entered into the database and double-checked for accuracy by a team member blind to participant allocation. An audit of the data will be completed by a senior member of the research team in 3 months. All information obtained during the trial will be kept in a locked cabinet or on a password-protected computer and destroyed (deleted or shredded) after 15 years.

#### Access to data and dissemination

All personal health information will be kept confidential and only accessed by the research team, unless required by law. This includes an audit by the Canadian College of Naturopathic Medicine Research Ethics Board, the Sunnybrook Health Sciences Center Research Ethics Board, or Health Canada Natural and Nonprescription Health Products Directorate. All data will be maintained on password-protected, secure servers or locked filing cabinets for the required length of time. Following this time, data will be destroyed securely by deleting the digital files or shredding paper documents. No identifying information from any participant will be used in the dissemination of study results. Dissemination of the study findings will occur through publication in open-access journals. Study participants will have the option to be notified of the study findings.

## Discussion

Given the prevalence of PDA and its resulting impact on quality of life and infant well-being, the importance of investigating underutilized and overlooked nonpharmacological options is paramount. Specifically, the need to investigate alternative approaches in comparison to prescription medication and psychotherapy has been identified as an important need by expecting and new mothers. It is anticipated that pregnant women with a history of depression and anxiety will be particularly interested in partaking in this trial, resulting in favorable recruitment rates. Given the positive findings of O3FA and probiotic supplements on mental health symptoms in nonpregnant adults, we expect a similar trend in PDA symptoms, with a low likelihood of adverse events.

While not our main objective, we anticipate a correlation between the microbial composition and probiotics and O3FA supplementation. As several recent studies have demonstrated a positive impact of probiotics (19–21) or O3FAs (22, 23) on mental health outcomes via changes in the gut microbiome, this has yet to be demonstrated in individuals at risk of PDA. Having intervention groups that provide both supplements (Gutboost) versus O3FA alone (Gutless) will allow us to determine potential interaction between these supplements. We anticipate a difference in mental health scores between the Gutboost and Gutless intervention groups. Incorporating a third intervention arm where dietary counseling is provided in addition to supplementation (Gutopia) further allows us to understand the interaction between diet and supplementation. We anticipate differences in mental health scores between Gutopia compared to the other intervention arms. Additionally, having an active control arm can potentially inform the magnitude and directionality of these changes by comparing outcomes in the intervention arms (*N* = 75) to the active control arm (*N* = 25).

Being the first feasibility trial to investigate probiotic supplementation and O3FAs for PDA symptoms, this study lays the foundation for larger, more powerful studies to further contribute evidence for the efficacy of this potential preventative treatment option. This type of evidence creates a rationale for the inclusion of nutrition professionals in mental healthcare teams and the use of dietary counseling in the treatment of PDA. Nutrition interventions can be low-risk, acceptable to patients, cost-effective, and may have additional benefits to overall health, which is particularly important for our target population.

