**Methods:**

This is a single-centered, partially randomized, placebo-controlled, double-blind feasibility trial. One hundred pregnant women with a history of depression and/or anxiety/PDA will be recruited and randomized into one of four arms, which could include the following: receiving a daily dose of both investigational products and dietary counseling on increasing dietary fiber, receiving a daily dose of both investigational drugs only, receiving fish oil investigational product and placebo, and a control arm with no intervention. The study involves six study visits, all of which can be conducted virtually every 3 months from the time of enrollment. At all study visits, information on diet, mental health, physical activity, and sleep quality will be collected. Additionally, all participants will provide a stool sample at each visit.

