## Methods

### Trial design and setting

This is a single-centered, partially randomized placebo-controlled double-blind feasibility trial with three intervention arms (Gutopia, Gutboost, and Gutless) and one active control. In total, 100 pregnant women with a history of depression and/or anxiety/PDA attending Sunnybrook Hospital Clinics in the Greater Toronto Area will be recruited.

Participants in Gutopia will receive a daily dose of both investigational products and dietary counseling on increasing dietary fiber. Participants in Gutboost will receive a daily dose of both investigational supplements, while participants in the Gutless arm will receive fish oil and a placebo. Participants in Gutless and Gutboost will be blinded to the status of the placebo/probiotic they will be receiving. The study member interacting with the patients will also be blinded to the treatment group the participant is assigned to. Participants who fully consent to receiving both investigational products, including placebo, will be fully randomized to one of the intervention arms. Participants not willing or able to take a placebo or probiotics will be assigned (not randomized) to the appropriate group that accommodates their preferences/needs. Participants unable or unwilling to take any of our investigational products will be assigned to the active control arm. Women in the control arm will receive standard care offered to all obstetric patients seen at the hospital.

The study involves six study visits, all of which can be conducted virtually every 3 months from the time of enrollment (**Figure 1**). The last study visit will happen between 9 and 12 months postpartum. Two of the study visits will occur during pregnancy [enrollment (visit 1) and third trimester (visit 2)], with the remaining occurring at 1, 3, 6, and 9 months postpartum. At all study visits, information on diet, mental health, physical activity, and sleep quality will be collected. Additionally, all participants will provide a stool sample at each visit, using our stool collection kits, which will be shipped to or dropped off at our center.

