### Sample size, recruitment plan, and prestudy screening

While a consensus on an ‘ideal’ sample size for pilot/feasibility studies has not been reached, our proposed number (*N* = 100) meets the recommendation for best practice for the conduct of pilot trials.

This is a single-center study conducted at Sunnybrook Hospital, in Toronto, Canada. Pregnant patients attending obstetrics clinics or The Women’s Mood and Anxiety Clinic at Sunnybrook Hospital will be informed by their attending healthcare provider about the study, and permission to share their contact number with the research team will be requested. Interested patients will be called by a member of the research team and screened for inclusion/exclusion criteria and their ability/status on O3FA and probiotic intake. Patients not willing or unable to take either supplement will receive information about the control arm of the study. Patients willing to take the study supplements will receive information about the interventional arms of the study and the process of randomization. Participants will also be informed that they may receive a placebo instead of probiotics. This design accommodates patient preferences and expectations and emphasizes the goal of an inclusive, pragmatic study design to generate real-world data.

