#### Outcomes measured

As a feasibility study, process evaluation will be our primary outcome. In the first 6 months of the trial, we will monitor the number of patients screened, randomized, and enrolled per month; the average time lapse between screening and enrollment; and the time taken to enroll 15% of our target (i.e., *n* = 15). We will also assess baseline rates of O3FA and probiotics supplementation in this specific cohort prior to randomization. We will identify and document all barriers to meeting the target numbers needed for each study arm and address them appropriately. In patients successfully enrolled, we will also monitor compliance, side effects, and challenges in taking supplements in the intervention groups. We will closely document all issues in adhering to intake instructions and attempt to resolve them on a case-by-case basis (i.e., if forgetfulness is a cause, daily automatic email reminders will be sent to that individual). In Gutopia, attaining a daily fiber target of 35 g/day will be monitored frequently via phone call in the first 6 months or until the patient no longer needs the support. Finally, we will assess retention rates, the proportion of study visits completed, and challenges related to the collection and shipment of stool samples, as well as the completion of questionnaires and dietary recall. All barriers to the timely completion of these tasks will be documented and managed on a case-by-case basis. Strategies to overcome each of these barriers will be proposed in the final write-up of this study.

As part of our secondary aims, we will seek the opportunity to produce preliminary data on the association between maternal microbial response to each intervention and self-reported scores on questionnaires of mental health challenges. This will be for exploratory purposes to identify any signals that will further support the conduct of a larger trial.

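### The Abstract says all 100 women are randomised across four arms, but under the Methods nobody is randomised to control and, on the article's own 75/25 split, at most 75 are randomised at all

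*Protocol article*

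**What the plan says.** The Abstract (Methods) opens with the design label: "This is a single-centered, partially randomized, placebo-controlled, double-blind feasibility trial". The next sentence gives the allocation: "One hundred pregnant women with a history of depression and/or anxiety/PDA will be recruited and randomized into one of four arms". It then lists the four arms, the last being a control arm without intervention.

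Trial design and setting gives a three-way rule:

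- Women who agree to both products, placebo included, "will be fully randomized to one of the intervention arms".
- Women who will not or cannot take a placebo or a probiotic are placed, explicitly without randomisation, in an arm that suits them.
- "Participants unable or unwilling to take any of our investigational products will be assigned to the active control arm".

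Three other sections agree. Sample size, recruitment plan, and prestudy screening directs women to control or to the intervention arms by willingness to take the supplements. Randomization and baseline evaluation says women are randomised or assigned according to their screening answers. The stratification paragraph under Exclusion criteria specifies permuted blocks of three and six.

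On size, the sample size section says "our proposed number (*N* = 100) meets the recommendation for best practice for the conduct of pilot trials". Outcomes measured mentions "barriers to meeting the target numbers needed for each study arm". The Discussion expects the control arm to inform the magnitude and direction of changes by "comparing outcomes in the intervention arms (*N* = 75) to the active control arm (*N* = 25".

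**The concern.** A reader of the Abstract would take this as a four-arm randomised trial of 100 women with a randomised control group. That reader would then treat the Discussion's 75-versus-25 comparison as protected by randomisation. Under the Methods it is not. Control consists of women who declined or could not take every product, so they may differ from the others in attitude to supplements, health behaviour or reasons for refusal, whatever the interventions do.

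The matter is more than editorial here. Numbers screened, randomised and enrolled are primary process outcomes, and the results are meant to shape a larger trial. How many women accept randomisation is itself a feasibility result, and the Abstract presents acceptance as universal. The efficacy analysis outlined for a continued trial compares arms by group membership, so the distinction between randomised and placed women needs to be clear from the outset.

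**Working it through.** **Inputs.** Total 100 (Abstract; sample size section). Intervention 75, control 25 (Discussion). Three intervention arms, randomisation only among these, control by unwillingness or inability only (Trial design and setting). Blocks of 3 and 6 (Exclusion criteria).

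**1. The plan's own figure.** 75 + 25 = 100, and 75 / 3 = 25 per intervention arm if equal. The split is internally consistent.

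**2. Number randomised under the Methods.** Let C be the number in control and A the number placed in intervention arms by preference. Then

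randomised = 100 − C − A, and randomised to control = 0.

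With C = 25, randomised = 75 − A, which is at most 75. All 100 could be randomised only if C = 0 and A = 0, which leaves the fourth arm empty. The Abstract's sentence therefore cannot hold together with a control arm of any size.

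**3. Block sizes.** 3 and 6 are both multiples of three. Neither is a multiple of four (6 / 4 = 1.5). The blocks suit equal randomisation among three arms, as Trial design and setting describes, and not among four.

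**4. Illustration of A.** The documents give no refusal rates, so these shares are assumptions only.

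| Share of the 75 placed by preference (assumed) | Placed | Randomised | Randomised per arm |
|---|---|---|---|
| 0% | 0 | 75 | 25 |
| 20% | 15 | 60 | 20 |
| 40% | 30 | 45 | 15 |

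For scale, the 95% half-width for a difference between two arm means is 1.96 × √(2/n) SD: 0.55 at n = 25, 0.62 at n = 20 and 0.72 at n = 15. The article claims no precision, so these figures contradict nothing in it. They show only why the randomised count should be given separately.

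**5. Can 75/25 be reached?** Let p be the assumed share of eligible, consenting women who decline everything. If the first 100 were enrolled with no target per arm, expected control size would be 100p: 10 at p = 0.10, 25 at p = 0.25, 40 at p = 0.40. If arms are instead recruited to targets, about 25 / p women are needed to fill control: 250 at p = 0.10, 125 at p = 0.20. The split then costs more approaches but is reachable.

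**The case against.** The strongest reply is that the article discloses its design. The Abstract calls the trial partially randomised in the sentence just before the faulty one, the Methods repeat the label and set out the rule, and Randomization and baseline evaluation already uses the accurate wording. On this view one loose sentence misleads nobody who reads on. No stated power, effect size or interval width depends on it, and the primary outcome is process evaluation.

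Much of that stands. No power claim is undermined, and the correct account is in the article. But the label does not repair the sentence that follows it: that sentence still gives all 100 women, control included, as randomised, and so conflicts with the label as well as with the Methods.

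Three stronger readings are tempting and are not supported:

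- *That the design cannot deliver 75 and 25.* Outcomes measured refers to target numbers for each arm, and a non-randomised arm can be recruited to a target.
- *That the absence of a rule for closing control at 25 is a fault.* That is operational detail an article may leave to the full protocol, which is not shown.
- *That Gutboost versus Gutless is the only randomised contrast.* Women who accept everything are randomised to any of the three intervention arms, so both contrasts involving Gutopia are equally randomised among them.

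**Conclusion.** The point holds as an inconsistency in a stated size and design property. The Abstract's randomised total of 100 over four arms is wrong as written. On the Discussion's split the maximum is 75, over three arms, with none randomised to control; the shortfall is at least 25 women, plus any placed by preference within the intervention arms. This rests only on the article's own allocation rule and its 75/25 figures, with no outside assumption.

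It follows that intervention versus control is a non-randomised comparison, and that the three contrasts among intervention arms are randomised only within women who accepted both products and placebo. How far below 75 the randomised number falls is unknown; the 20% and 40% cases are illustrations. The 75/25 split is arithmetically sound and not shown to be unattainable. The correction is modest but worth making, because the Abstract is what most readers will rely on.

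**What to change.** - In the Abstract, replace the statement that all 100 are randomised to four arms with one saying they are recruited and then randomised or assigned, in line with Randomization and baseline evaluation. Add that at most 75 are randomised, among the three intervention arms.
- In the Discussion, label 75 and 25 as recruitment targets and describe intervention versus control as a non-randomised comparison.
- Commit to reporting, for each intervention arm, the randomised and the preference-assigned women separately, so that contrasts among the intervention arms can be read within the randomised set.

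The cost is a few sentences and one extra split in the participant flow figures. No participants, visits or design changes are needed. The stated randomised size becomes less favourable, but it will be correct.
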